**Figure 1 F1:**
[figure not shown]
**Course outline showing distance and direction taken by participants, during the 30 s HIT protocol**. A = 10 m, B = 20 m, C = 10 m.

Group B (n = 24) will be instructed to exercise at an intensity of 70% VO_2 _max (moderate) [48], running steadily for a period of 20 mins. The speed of exercise will be determined by the participant's performance in the 20-m shuttle test (MSFT) [49]. During week 4 all participants will be instructed to perform the 20MST to determine any training effect. Upon analysing the participant's performance in week 4, week's 5 - 7 will see the participants instructed to exercise at an intensity that elicits 70% of predicted VO_2_max, running steadily for 20 mins. Finally, RPE using the 15 point scale [50] and mood state will be measured upon the completion of each exercise session.

The intervention will be carried out during the lunch hour or PE lessons, on Monday, Wednesday and Friday, and for a period of 7 weeks. The intervention will be performed in the school sports hall during October through December, 2009, to allow for uninterrupted use of the facilities. Each training day will be supervised by two members of the PE department and at least one researcher. This will ensure that participants continue exercising at the pre-determined intensity. Participants will be instructed to wear appropriate footwear whilst taking part in the intervention. Attendance will be monitored by the researcher on all days when the intervention is scheduled to take place.

### Measurements

All measurements will be performed pre- and post-intervention for both intervention and control groups. In addition, the vertical jump, 10 m sprint, 20MSFT and the 505-agility test will also be taken at the end of week 4 in the intervention group. All measurements will be carried out by experienced individuals during normal PE lessons and on school premises to ensure minimal disruption to the curriculum. Finally, all individuals involved in performing measurements will be CRB checked prior to the commencement of the study.

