### Data Analysis

A pre- and post-intervention design will be used to compare differences in measured outcomes between participants assigned to the control group and the intervention groups. Initially, baseline data will be used to perform Pearson's product moment correlation coefficients, followed by multiple regression analysis to estimate the significance of selected predictors on CVD risk factors. Statistical significance will be set at *P *= 0.05.

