### Intervention

Participants involved in the intervention will be assigned to groups A or B by a third party using computer generated sequences of random numbers. The research team and the participants will be blinded to the randomization process, and assignment to groups will only be disclosed after baseline testing. All participants will be instructed not to change their dietary or lifestyle habits other than prescribed. The secondary 5 participants will act as the control group and will be assigned to group C (*n *= 24). Participants will be encouraged to continue their regular PA patterns.

Group A (*n *= 24) will be instructed to complete a 30 seconds (s) maximal effort sprint within a 20 m distance separated by cones (see Figure 1). The start point will be located at the mid-point of the markers. Participants will be instructed to sprint from the midpoint to the first marker, turn, and then sprint 20 m in the opposite direction to the second marker. Thereafter, participants will turn and run again through the midpoint covering a total distance of 40 m. Though this protocol has been used and validated as a measure of anaerobic performance [47], in this study, participants will be instructed to sprint maximally for a period of 30 seconds. Following 30 s rest, the participants will be instructed to repeat this procedure a further 3 times. This equates to 2 minutes (mins) of maximal effort sprinting interspersed with 2 mins recovery. Participants will be requested to perform this protocol 3 times weekly. Training progression will be implemented by increasing the number of repeats from four repetitions during weeks 1 and 2, to five repetitions during weeks 3 and 4, to six repetitions during weeks 5 and 6. Finally, during week 7 participants will still perform six repetitions but interspersed by only 20 s recovery. Prior to the commencement of the training regime, participants will be given a familiarization trial of four low intensity runs under test procedures.

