#### Physiological measurements

Systolic and diastolic blood pressure (BP) measurements will be taken using an automated BP monitor (Omron Healthcare UK Ltd, Milton Keynes, UK) after each participant has sat quietly for a period of 10 mins. The cuff will be placed tightly on the upper left arm of the participant with three measurements taken to ensure accuracy. An average of the second and third measures will then be recorded and used for the data analysis [52].

Physical fitness is well established as a marker of health status in youth [6]. Thus, the health related physical fitness components of muscular strength, speed, agility and cardiorespiratory fitness will be measured prior, during and after the intervention.

Heart rate (HR) response will be measured on all participants at the end of each training week through the use of continuous heart rate telemetry (Hosand, TM200, Hosand Technology, Verbania, Italy). The rationale for this will be two fold. Firstly, from this recording the average intensity of each training session will be estimated as a function of a percentage of the theoretical HR peak, in accordance with standard procedures [53]. Secondly, during each weekly session a projector will beam the HR responses onto a wall in the sports hall. Thus all participants will be able to monitor their own HR response during, and after, the exercise session. Upon completion of the exercise session participants will be provided with personalized feedback and will be encouraged to ask questions. Based on previous literature [54,55], it is expected that this personalized feedback will encourage engagement and adherence with the intervention and aims of the study.

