Aerobic fitness will be measured through the use of the 20MSFT [49]. The 20MSFT has been validated as a predictor of maximal aerobic power in young people [56] and is familiar with all youth. Participants will be instructed to run between two lines separated by 20 m, while keeping pace with the audio signals emitted from a CD produced by the National Coaching Foundation. The initial speed will be set at 8.5 km/hr which will increase by 0.5 km/hr each minute (1 minute equates to 1 level). All participants will be instructed to continue for as long as possible until they have reached their maximal effort. Otherwise, the test will end when the participant fails to reach the end lines before the audio signal on two consecutive occasions. The CD will be calibrated over a 1 minute duration before its use. Finally, participants will be instructed to complete a standardized warm up and cool down comprising of light jogging and stretching before and after the test and each training session.

The counter movement jump test will be used to measure explosive muscular power. Jumping height will be measured through the use of the Optojump system (Microgate, Bolzano, Italy) after a standardized warm up. Participants will begin in a standing position with their feet shoulder width apart. Thereafter, they will be instructed to perform a counter - movement with their legs prior to jumping. Each participant will be instructed to perform three jumps with a minimum of two mins recovery between each effort. The best of the three jumps (to the nearest cm) will be used as the criterion measure. Participants will be instructed to keep their hands on their hips throughout all jumps, to give maximal effort and land in an extended position. Muscular strength will be measured by the number of completed push ups in 30 s [57].

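### Four fitness tests are repeated at week 4 in the training groups only, so any retest effect is confounded with group in the comparison with control

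*Protocol article*

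**What the plan says.** The Measurements section first sets a common schedule: "All measurements will be performed pre- and post-intervention for both intervention and control groups". It then adds an interim session for some pupils only: the jump, the short sprint, the shuttle run and the agility test "will also be taken at the end of week 4 in the intervention group".

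The Data Analysis section describes a pre/post design intended to "compare differences in measured outcomes between participants assigned to the control group and the intervention groups". The Intervention section defines the control arm: "The secondary 5 participants will act as the control group and will be assigned to group C". Those pupils come from a younger school year and are not randomised.

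Two other statements touch on week 4:

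- In the Intervention section, the group B paragraph after Figure 1 says "During week 4 all participants will be instructed to perform the 20MST to determine any training effect".
- The Physiological measurements section says that the fitness components "will be measured prior, during and after the intervention", without naming a group.

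The same section says that the shuttle run "is familiar with all youth". It scores the jump, 10 m sprint and 505 tests as the best of three attempts within a session.

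**The concern.** All four tests call for maximal effort and depend partly on technique or pacing. If having done a test once more changes the score, that change falls on groups A and B and not on group C. Exposure then coincides exactly with the trained-versus-control contrast, so no analysis of these data can separate a testing effect from a training effect.

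Aerobic profile and physiological responses to the high-intensity programme are both listed among the primary objectives. Part of a reported gain over control on these tests could therefore be a product of the test schedule. The article describes no matching control session and no familiarisation session for these tests. The one familiarisation trial in the Intervention section is for the sprint-training course.

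**Working it through.** **Test sessions completed by the end of post-test**

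| Measure | Groups A and B | Group C |
|---|---|---|
| Jump, 10 m sprint, shuttle run, 505 | 3 (pre, week 4, post) | 2 (pre, post) |
| Blood pressure, blood markers, anthropometry | 2 | 2 |

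This reads the intervention group in the Measurements section as both A and B, and the week-4 shuttle sentence as not reaching group C.

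**The plan's own sample size.** The Sample size section gives d = 0.50, power 0.80, p = .05, 17 per group, and 24 after 30% drop-out. One set of assumptions reproduces 17: a group-by-time interaction, 2 groups, 2 occasions, f = d/2 = 0.25 and a pre-post correlation of 0.5 (assumed).

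- λ = f² × N × m / (1 − ρ) = 0.0625 × 34 × 2 / 0.5 = 8.5 on 1 and 32 degrees of freedom, giving power 0.807.
- 17 / 0.7 = 24.3, against the 24 stated.

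So 17 per group is a reasonable basis for what follows.

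**Size of the possible distortion.** The document gives neither a retest effect nor a correlation. Assume:

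- a net effect b of the extra session of 0.1, 0.2 or 0.3 baseline SD, in the trained group only;
- no true training effect and no other bias;
- pre-post correlation ρ of 0.5 or 0.8;
- two-sided 5% test (sidedness is not stated) comparing one training group with control on change scores, n = 17 each.

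Formulas, in baseline SD units:

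- SE = √[2(1 − ρ) × 2/n]. At ρ = 0.5: √(1.0 × 2/17) = 0.343. At ρ = 0.8: √(0.4 × 2/17) = 0.217.
- Noncentrality = b / SE. For b = 0.2: 0.2/0.343 = 0.58 and 0.2/0.217 = 0.92.
- Rejection probability = P(|t| > 2.037), from the noncentral t with 32 degrees of freedom.

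| b (SD) | ρ = 0.5, two-sided | of which favouring training | ρ = 0.8, two-sided | of which favouring training |
|---|---|---|---|---|
| 0 | 5.0% | 2.5% | 5.0% | 2.5% |
| 0.1 | 5.9% | 4.7% | 7.3% | 6.5% |
| 0.2 | 8.7% | 8.2% | 14.5% | 14.3% |
| 0.3 | 13.6% | 13.3% | 26.9% | 26.8% |

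The distortion grows with ρ because a more precise analysis detects the artefact as readily as it would a true effect. More pupils do not help either: with all 24 per group retained and ρ = 0.8, the two-sided figures are 8.4%, 18.9% and 36.3%.

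**Relative to the target.** If d = 0.50 is read as a between-group difference in change, 0.1 to 0.3 SD is 20 to 60% of it. The interaction formula that reproduces 17 implies a difference in change of 4 × 0.25 = 1.0 SD; on that reading the share is 10 to 30%.

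**The case against.** Several counter-arguments carry weight.

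- **Direction.** A reader might infer that the extra session always flatters training. The document does not show that. On maximal-effort tests, lower motivation at a third attempt could act the other way. Favouring training is the likelier direction, but it is an assumption.
- **Existing practice.** The shuttle run is described as already familiar, and best-of-three scoring gives every pupil, controls included, three attempts at baseline on the other three tests. The contrast is a third session against a second, not practised against unpractised. This may shrink the effect but does not equalise exposure.
- **Training as practice.** Group A performs maximal sprints with turns three times a week for 7 weeks, 3 × 7 = 21 sessions. Much task familiarity in sprinting and turning is thus part of the intervention, and a week-4 test for controls would not remove it. That stands, but it is no reason to add an avoidable difference in the testing itself.
- **Contradiction.** A reader might infer that the Intervention and Measurements sections contradict each other on who runs the week-4 shuttle test. The sentence in question lies between two statements on group B's running intensity. The Physiological measurements section likewise refers to all participants for heart rate at the end of each training week, which fits only pupils who train. It is an ambiguity more than a contradiction. If controls were meant, the shuttle run would be balanced and the imbalance would remain for the other three tests.
- **Larger bias elsewhere.** The non-randomised, younger control year is a separate and possibly larger bias. That is fair: equal testing would not make this comparison unbiased.

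**Conclusion.** The concern holds in a limited form. The document itself fixes one more test session for trained pupils than for controls on four tests, and nothing else in it offsets this. The comparison with control on those tests therefore mixes any retest effect with the training effect.

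The size is unknown. The rates of about 6 to 14% (ρ = 0.5) and 7 to 27% (ρ = 0.8) rest on assumed retest effects of 0.1 to 0.3 SD, 17 per group, a two-sided change-score test and an otherwise unbiased comparison. They illustrate sensitivity and do not estimate the trial's error rate.

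The point should not be extended to the cardiovascular risk results as a whole. Blood pressure, blood markers and anthropometry have no week-4 repeat. The randomised comparison of A with B is also unaffected, provided that both are tested at week 4; the singular wording "will also be taken at the end of week 4 in the intervention group" leaves this to be confirmed. The point is worth acting on because the imbalance can be removed at small cost.

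**What to change.** **Preferred:** give group C the same four tests at the end of week 4 and state in the Measurements section that all three groups are tested. The cost is one or more PE lessons for 24 pupils, with equipment already in use. More than one may be needed, since three of the tests take three attempts each, two of them with at least 2 minutes between efforts, and the shuttle run is maximal. The sample size does not change.

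**If the school cannot spare the time:** keep only the week-4 shuttle run, which is used to reset group B's speed. Drop the week-4 jump, 10 m sprint and 505 tests in groups A and B. Report the shuttle-run comparison with control as subject to unequal test exposure. The cost is the interim data on three tests.

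**In either case:** clarify in the group B paragraph of the Intervention section which pupils the week-4 shuttle sentence covers, and in the Measurements section that the intervention group means both A and B.

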#### Anthropometrics

Stature will be measured without shoes to the nearest millimetre with the use of a transportable stadiometer (Seca Stadiometer, Seca Ltd, Birmingham, UK). Body mass will be measured in normal PE clothing to the nearest 0.1 kg using a calibrated electronic weighing scales (Seca 880, Digital Scales, Seca Ltd, Birmingham, UK). Body mass index (BMI) will then be calculated by dividing the participants weight by their height squared. Waist and hip circumference will be measured on each participant in an upright position by using anthropometric tape (Rosscraft, UK). Waist circumference will be taken from the narrowest part of the trunk at the end of a gentle expiration. Hip circumference will be taken around the maximum protrusion of the buttocks. Body fat percentage will be estimated from skinfold measurements taken at two sites (triceps and calf) in accordance with standard procedures [51]. A third skinfold measurement will be taken if the first two measurements differ by more than 1.0 mm.

#### Physiological measurements

Systolic and diastolic blood pressure (BP) measurements will be taken using an automated BP monitor (Omron Healthcare UK Ltd, Milton Keynes, UK) after each participant has sat quietly for a period of 10 mins. The cuff will be placed tightly on the upper left arm of the participant with three measurements taken to ensure accuracy. An average of the second and third measures will then be recorded and used for the data analysis [52].

Physical fitness is well established as a marker of health status in youth [6]. Thus, the health related physical fitness components of muscular strength, speed, agility and cardiorespiratory fitness will be measured prior, during and after the intervention.

Heart rate (HR) response will be measured on all participants at the end of each training week through the use of continuous heart rate telemetry (Hosand, TM200, Hosand Technology, Verbania, Italy). The rationale for this will be two fold. Firstly, from this recording the average intensity of each training session will be estimated as a function of a percentage of the theoretical HR peak, in accordance with standard procedures [53]. Secondly, during each weekly session a projector will beam the HR responses onto a wall in the sports hall. Thus all participants will be able to monitor their own HR response during, and after, the exercise session. Upon completion of the exercise session participants will be provided with personalized feedback and will be encouraged to ask questions. Based on previous literature [54,55], it is expected that this personalized feedback will encourage engagement and adherence with the intervention and aims of the study.

Aerobic fitness will be measured through the use of the 20MSFT [49]. The 20MSFT has been validated as a predictor of maximal aerobic power in young people [56] and is familiar with all youth. Participants will be instructed to run between two lines separated by 20 m, while keeping pace with the audio signals emitted from a CD produced by the National Coaching Foundation. The initial speed will be set at 8.5 km/hr which will increase by 0.5 km/hr each minute (1 minute equates to 1 level). All participants will be instructed to continue for as long as possible until they have reached their maximal effort. Otherwise, the test will end when the participant fails to reach the end lines before the audio signal on two consecutive occasions. The CD will be calibrated over a 1 minute duration before its use. Finally, participants will be instructed to complete a standardized warm up and cool down comprising of light jogging and stretching before and after the test and each training session.

The counter movement jump test will be used to measure explosive muscular power. Jumping height will be measured through the use of the Optojump system (Microgate, Bolzano, Italy) after a standardized warm up. Participants will begin in a standing position with their feet shoulder width apart. Thereafter, they will be instructed to perform a counter - movement with their legs prior to jumping. Each participant will be instructed to perform three jumps with a minimum of two mins recovery between each effort. The best of the three jumps (to the nearest cm) will be used as the criterion measure. Participants will be instructed to keep their hands on their hips throughout all jumps, to give maximal effort and land in an extended position. Muscular strength will be measured by the number of completed push ups in 30 s [57].

Sprint speed will be measured over 10 m and 50 m through the use of an electronic sprint timer with photoelectric sensors (Polifemo Radio Light - Microgate, Italy). The 10 m sprint will take place in the school sports hall with the photoelectric sensors being placed at 0 and 10 m intervals. Participants will be instructed to perform each sprint from a standing start. All participants will complete three trials with the fastest time (to the nearest 0.01 s) being used as the criterion measure. Due to area restrictions, the 50 m sprint will take place outdoors on an artificial turf soccer field with the photoelectric sensors being placed at 0 and 50 m intervals. Participants will be instructed to perform each sprint from a standing start. All participants will complete three trials with the fastest time (to the nearest 0.01 s) being used as the criterion measure.

Agility will be measured through the use of the 505 test [58]. Two photoelectric sensors (Polifemo Radio Light - Microgate, Italy) will be placed 5 m from the starting line and 5 m from a designated turning point. Participants will be instructed to sprint maximally to the designated turning point, pivot, and then return as quickly as possible through the photoelectric sensors in accordance with standard procedures [58]. Participants will be instructed to perform three sprints with a minimum of 2 mins recovery between each effort. Times will be measured to the nearest 0.01 s with the fastest value obtained from the three efforts used as the criterion measure.

#### Blood sampling and analysis

Blood samples will be collected between 9:00 am and 11:00 am after an overnight fast. Prior to sampling participants will be instructed to sit quietly for a period of at least 30 mins to control for plasma volume shifts [59]. A team of qualified phlebotomists, experienced in paediatric sampling techniques will take blood samples from the participants. Participants will be provided with breakfast in the school canteen once sampling is complete. The samples will be analyzed for total cholesterol (TC), insulin, high-density lipoprotein (HDL), high-sensitivity C-reactive protein (hs-CRP), glucose, fibrinogen (Fg), interleukin-6 (IL-6), adiponectin (high molecular weight), triglyceride and plasminogen activator inhibitor-1 (PAI-1). Within four hours all blood samples are to be transported to the laboratory where they will be aliquoted and frozen at - 80°C.

#### Questionnaires

All participants will be instructed to complete the physical activity questionnaire for adolescents (PAQ-A). This validated questionnaire has been used in previous research [60] with participants instructed to recall their PA behavior from the previous 7 days. From previous experience we envisage that completion of the questionnaire will take no longer than 30 minutes and thus can be completed during scheduled class time. Sexual maturation status will be determined through the use of a self-reported questionnaire [61]. Participants will be asked to indicate their current stage of development regarding their pubic hair and genital development. Health related quality of life (HRQOL) will be measured through the use of the paediatric quality of life inventory (PedsQL™) for both the participant and their parent/guardian [62]. The PedsQL™ has been shown to be a valid and reliable instrument specifically developed for use with children and adolescents [63]. The brief one page instrument has 23 questions and covers four dimensions: physical functioning, emotional functioning, social functioning and school functioning.

